**Inclusion criteria**
Diagnosed with Grade I or Grade II WAD
Report an average neck pain since the accident of at least 3 on a 0–10 "Numerical Rating Scale" (NRS)
Able to give written informed consent and complete interviews in English (translators will be available to assist the participant if she/he experiences difficulty understanding specific items on the questionnaire)
Make an insurance claim for physical injury and enroll in trial within 21 days of the traffic collision

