### Randomization to treatment groups

Participants will be randomly allocated to one of the three intervention arms after they complete the consent process and answer the baseline questionnaire. If passengers from the same motor vehicle agree to participate, they will be randomized to the same treatment arm to minimize contamination and potentially minimize cross-over between treatment arms. Therefore, our unit of randomization is the motor vehicle. Central randomization was performed by the study biostatistician using statistical package, NQuery Advisor^® ^7.0.[19] To minimize the risk of unbalanced treatment assignment related to patient heterogeneity, we used block randomization which was stratified by clinical centre. The size of the blocks was randomly determined and vary between three, six, nine and 12 participants. The biostatistician provided the trial coordinators with a series of sealed opaque envelopes sequentially numbered by clinical centre. The study biostatistician is not involved in the selection of participants.

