### Data collection and follow-up

Table 2 summarizes the data to be collected during the trial. We will follow-up participants at six weeks, and three, six, nine and 12 months post-injury. All follow-up interviews will be conducted by a research assistant either in person at the study clinic or by telephone. The study research assistant will be blind to the treatment allocation and to the baseline characteristics of participants. However, because most outcomes are self-reported by the participants, the research assistant will not be blind to their outcomes status.

**Table 2 T2:** Measures used at baseline and follow-up interviews

**Measures**	**Baseline**	**6 Weeks**	**3 Months**	**6 Months**	**9 Months**	**12 Months**
Accident information	x					

Past history of neck pain and whiplash	x					

Numerical rating scale	x	x	x	x	x	x

Health care after accident	x					

Comorbidity questionnaire	x					

Acute 36-item short-form health survey (V2)	x	x	x	x	x	x

Work status	x	x	x	x	x	x

Expectation of recovery	x	x	x	x	x	x

Whiplash disability questionnaire	x	x	x	x	x	x

Center for epidemiological studies-depression scale (CES-D)	x	x	x	x	x	x

Vanderbilt pain management inventory	x	x		x		

Health state question	x	x	x	x	x	x

Socio-demographic characteristics	x					

Whether a lawyer or paralegal is involved in the claim	x	x	x	x	x	x

Global perceived recovery question	x	x	x	x	x	x

Satisfaction with care and treatment outcome		x	x	x	x	x

Co-interventions		x	x	x	x	x

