### Outcomes

#### Primary outcomes

##### Time to recovery

Our primary outcome is time to recovery measured by the global self-perceived recovery question. The global perceived recovery question is a reliable, valid and responsive measure of health status in patients with musculoskeletal disorders.[21] This ordinal transition scale has been used in previous randomized trials and cohort studies of neck pain.[11,22,23] In patients with WAD, we have previously reported that perceived recovery is consistently associated with less neck pain, better physical functioning and fewer depressive symptoms.[11]

At each follow-up interview, participants will be asked: "How well do you feel you are recovering from your injuries?" Participants will select between one of the seven following choices: 1) completely better; 2) much improved; 3) slightly improved; 4) no change; 5) slightly worse; 6) much worse and 7) worse than ever. Participants who respond to be "completely recovered" or "much improved" will be considered recovered. Time to recovery will be measured as the number of days between the date of injury and the first follow-up date at which a participant reports to be "completely recovered" or "much improved".

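### Participants who already meet the recovery definition at baseline are counted as post-randomization recoveries, which can dilute the hazard ratio by an amount the documents do not let one fix

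*Protocol article*

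**What the plan says.** Under Time to recovery, the Protocol article defines the event by the two best answers to a seven-level question and times it from the date of injury to "the first follow-up date at which a participant reports to be" in one of those two categories. Only follow-up answers can be events.

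Table 2 (Data collection and follow-up) lists the "Global perceived recovery question" at baseline as well as at every follow-up. Under Randomization to treatment groups, participants are allocated "after they complete the consent process and answer the baseline questionnaire", so the baseline answer precedes allocation.

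The pain criterion in Table 1 is "Report an average neck pain since the accident of at least 3 on a 0–10" scale, and participants must "enroll in trial within 21 days of the traffic collision". No inclusion or exclusion criterion concerns current pain or perceived recovery.

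The Statistical analysis section analyzes everyone as randomized. Under Primary outcomes: self-perceived recovery, a baseline characteristic becomes a candidate covariate if it varies between the arms, and is retained if it shifts an intervention coefficient by 10% or more. Baseline recovery status is not mentioned.

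**The concern.** An average since the accident can be 3 or more in someone who hurt badly in the first days and feels much improved by day 15 or 20. That person is eligible, meets the recovery definition before any trial treatment, and stays in the risk set. If the answer is the same at six weeks, the plan records a recovery in whichever arm was assigned.

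If such people are enrolled in similar proportions in each arm, they add events at the first visits that carry little or no information about treatment. That pulls the hazard ratio toward 1 and costs power. The information needed to separate them is already collected before allocation, so using it does not disturb the randomized comparison.

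**Working it through.** **1. The plan's own figure.** The Sample size section gives 114 per arm for 90% power, two-sided 0.05, a log-rank test and a 20% difference in one-year recovery. It gives no control rate, so 114 cannot be derived from the stated inputs alone. It can be reached for an absolute difference of 20 points. With HR = ln(1 − pT)/ln(1 − pC) and Freedman's events = (1.96 + 1.2816)² × [(HR + 1)/(HR − 1)]²:
- 20% vs 40%: HR = ln 0.60/ln 0.80 = 2.289; events = 10.51 × (3.289/1.289)² ≈ 68.4, so 69; 69/(2 × 0.30) = 115 per arm.
- 55% vs 75%: HR = ln 0.25/ln 0.45 = 1.736; events = 10.51 × (2.736/0.736)² ≈ 145.2, so 146; 146/(2 × 0.65) ≈ 113 per arm.

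Both are close to 114, so both serve as scenarios.

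**2. What the 20 points refer to.** Let q be the share recovered at baseline, which is assumed because the documents give no figure.
- *Not-yet-recovered reading:* the 20 points apply to the remaining 1 − q. The difference among all enrolled is then (1 − q) × 20, which is 19, 18 and 16 points at q = 5%, 10% and 20%.
- *All-enrolled reading:* the 20 points hold overall. The rates among those not yet recovered are then (p − q)/(1 − q). For 55% vs 75% at q = 10% this gives 0.45/0.90 = 50% and 0.65/0.90 = 72%.

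**3. Simulation.** Two arms of 114; exponential recovery grouped at days 42, 91, 182, 273 and 365; two-sided 5% log-rank test. Everyone recovered at baseline is assumed to complete the six-week interview and report recovery again. Most cells used 4,000 replicates (Monte Carlo error about √(0.9 × 0.1/4000) ≈ 0.5 points). A repeat with 40,000 agreed to within about one point and supplied the all-enrolled cells at 2%.

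Power (%) with the analysis as planned:

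| Scenario and reading | q = 0 | 2% | 5% | 10% | 20% |
|---|---|---|---|---|---|
| 20 vs 40, not yet recovered | 92 | 90 | 85 | 78 | 63 |
| 55 vs 75, not yet recovered | 91 | 90 | 88 | 85 | 74 |
| 20 vs 40, all enrolled | 92 | 91 | 91 | 89–90 | n/a |
| 55 vs 75, all enrolled | 91 | 91 | 90–91 | 88 | 86–87 |

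(n/a: at q = 20% the control rate among those not yet recovered would be zero.)

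**4. Hazard ratio, not-yet-recovered reading** (Cox fit with Efron ties). At q = 0, 5%, 10% and 20% it is 2.26, 2.00, 1.82 and 1.57 for 20 vs 40, and 1.74, 1.67, 1.59 and 1.50 for 55 vs 75.

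**5. Would the covariate rule catch it?** At q = 10%, separating the recovered group moves the log hazard ratio from ln 1.82 = 0.599 to ln 2.26 = 0.815 (36%), or from ln 1.59 = 0.464 to ln 1.74 = 0.554 (19%). Either exceeds 10%. But the rule first requires the characteristic to differ between arms, and randomization tends to balance it. The dilution arises when it is balanced, so this first condition is what stops the adjustment.

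**6. Effect of stratifying.** Under these assumptions everyone in the recovered stratum has the event at the first visit, so that stratum adds nothing to the test and the result equals exclusion. On the not-yet-recovered reading, power at q = 5%, 10% and 20% is about 91%, 90% and 85% (20 vs 40), and 91%, 88% and 85% (55 vs 75). On the all-enrolled reading it is about 92%, 93% and 94% (55 vs 75), and about 98% for 20 vs 40 at q = 10%.

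**The case against.** The strongest reply is about size. The Sample size section speaks of a difference in one-year recovery and then of participants per group, which reads naturally as all enrolled participants. On that reading most of the apparent loss disappears, because the larger losses come largely from testing a smaller overall difference than planned. This stands, although the text does not settle the reading.

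Second, nothing in the documents shows that such people will be enrolled in numbers that matter. Entrants have diagnosed Grade I or II disorder, average pain of at least 3, an injury claim and willingness to be treated. This also stands: the criteria make such people less likely but do not exclude them.

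Third, a baseline answer is not an event. The person must complete a follow-up and still report recovery, and the trial's rationale is that early care influences recovery, so persistence could differ by arm. The simulation's full persistence and full six-week completion are therefore simplifications.

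Fourth, keeping everyone is consistent with the declared treatment-policy analysis, and strata are often left to an analysis plan. The first part is right, and the fix keeps everyone. The second carries less weight: the article itself fixes an event rule that ignores a pre-randomization measurement of the endpoint, and a covariate rule that would usually pass over it.

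A reader might infer that the stated 90% power is lost, that the comparison is biased between arms, or that median recovery time is understated. The documents support none of these. The power loss depends on an unknown prevalence; randomization still protects the comparison; and, because time runs from injury, an early improver is dated later than the actual improvement.

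**Conclusion.** The gap in the rule is real and can be read directly from the text: the endpoint is measured before allocation, eligibility does not depend on it, only follow-up answers count, and the adjustment rule would usually miss it. If participants already recovered at baseline are enrolled, the hazard ratio can be diluted toward 1.

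The size is conditional. At 114 per arm the power loss is about 2 points or less at 2% prevalence. At 5–10% it is about 1–3 points if the 20% difference applies to all enrolled participants, and about 3–14 points if it applies only to those not yet recovered. These figures assume an absolute difference of 20 points with control rates of 20% or 55%, similar prevalence in the arms, and full persistence and completion at six weeks. The plan's 114 is not shown to be wrong. The case for change rests less on the size of the loss than on the remedy: stratifying gave equal or higher power at every non-zero prevalence examined, under both readings.

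**What to change.** In the section Primary outcomes: self-perceived recovery, pre-specify that the primary log-rank and Cox comparison is stratified by the baseline answer to the global recovery question (the two recovered categories versus the rest), whether or not that answer is balanced between arms. State that all randomized participants remain in the intention-to-treat set. Report the number recovered at baseline by arm. Add a sensitivity analysis restricted to those not recovered at baseline. It would help to state in the Sample size section which population the 20% difference refers to.

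The cost is a few sentences and no new data, since Table 2 already schedules the item. The restricted analysis uses slightly fewer participants: at 10% prevalence, 114 × 0.90 ≈ 103 per arm. The rule should be fixed before outcomes are seen by arm, so that it is not a post hoc choice about the primary endpoint.

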#### Secondary outcomes

##### Neck pain intensity

Neck pain intensity will be measured at baseline and at each follow-up with the 11-point numerical rating scale (NRS). The NRS is a global measure of pain intensity anchored by two extremes of pain intensity ranging from 0 (referring to "No pain") to 10 (referring to "Pain as bad as it could be"). The NRS has good short-term test-retest reliability with correlation coefficient ranging from 0.95–0.99 when re-administered within 24 hours.[24] The NRS has good construct validity and can distinguish between various levels of pain in subjects with chronic post-operative pain.[24,25] It correlates well with other instruments used to measure pain.

##### Whiplash disability

Disability will be measured with the Whiplash Disability Questionnaire (WDQ).[26] The WDQ is a 13-item modified version of the Neck Disability Index. It includes 13 Likert scales scored from 0 to 10 with higher global scores indicating more disability. The instrument has adequate face validity, discriminate validity and good internal consistency (Cronbach's alpha = 0.96). [26,27] Pinfold et al. (2006)[26] reported that the WDQ has no substantial ceiling or floor effect. In patients with chronic stable symptoms, the WDQ has excellent short-term (24 hours) and medium-term (one month) reproducibility (Intra-correlation coefficient = 0.90, and 0.86, respectively).[28] The WDQ is a responsive scale with a minimal detectable change of 15 points.[28]

##### Health-related quality of life (H-RQoL)

We will use the Medical Outcomes Study Short-Form Health Survey version two (SF-36) to measure health-related quality of life. The SF-36 has 36 items which measure the H-RQoL of a subject. Two summary scores can be computed: the physical component score and the mental component score. There are eight individual scales: physical functioning, role physical, bodily pain, general health, vitality, social functioning, role emotional and mental health. The questionnaire has been shown to have excellent reliability demonstrated with internal consistency and test-retest methods. The SF-36 is a valid and reliable measure for clinical and general populations with a reported intra-class correlation coefficient of 0.85. [29-31] Further, in a study of injured workers with musculoskeletal conditions it was shown to be the instrument that is the most responsive to change.[32]

##### Depressive symptomatology

Depressive symptomatology in the previous week will be measured with the Center for Epidemiological Studies-Depression Scale (CES-D). The CES-D is a widely used 20-item self-report scale designed to measure current level of depressive symptomatology in population-based epidemiologic research.[3,33,34] It has good test-retest reliability and internal consistency and possesses good factorial and discriminant validity.[33,35-42] The CES-D is scored from 0 to 60 with higher scores indicating greater depressive symptomatology.[33,36]

##### Satisfaction with care and satisfaction with treatment

Two global questions will be used to quantify satisfaction with care and satisfaction with treatment outcome. Satisfaction with care will be measured by asking participants the following question: "All things considered, how satisfied are you with the care you received?" Similarly, satisfaction with treatment outcome will be measured by asking "All things considered, how satisfied are you with the results of your treatment?".[43,44] Participants will be asked to rate their satisfaction on a Likert scale ranging from 1 = extremely satisfied to 7 = extremely dissatisfied.

##### Time on insurance benefit

We will measure the number of days between the date of injury and the date corresponding to the closure of the insurance claim. Claim closure corresponds to the end of treatment, the attainment of maximal medical improvement, the termination of income replacement benefits or the date of payment of the last outstanding bill incurred by the claimant (e.g., eyewear). Claim closure dates will be provided by AVIVA Canada. We have previously validated time on benefit as a marker of time to health recovery in a population of whiplash patients from Saskatchewan and found that claimants who close their claims have significantly lower levels of neck pain, better physical functioning and no depression compared to claimants who have not closed their claim.[16]

##### Recurrence

A recurrence will occur when a participant reports to have recovered, but reports at any subsequent follow-up on the self-perceived recovery question to be: 1) slightly improved; 2) unchanged; 3) slightly worse; 4) much worse, or 5) worse than ever.

##### Co-interventions

We will measure co-interventions by asking participants to self-report the type health care provider consulted beyond those involved in delivering the trial interventions. Finally, we will ask participants if they have used medications for their whiplash injuries.

### Statistical Issues

#### Sample size

Our sample size was selected to detect a difference of 20% in the rate of recovery at one year using a log rank test, a power of 90% and a two-tail significance level of 0.05.[19] Based on these parameters, we need 114 participants per group. Assuming a 30% loss-to follow-up per arm we aim to enroll a total of 444 participants (148 per intervention arm).

It is common for vehicles involved in traffic collisions to have multiple passengers. Early in our trial, we observed that some participants enrolled in the study had a spouse or relative with them in the car at the time of the collision that was also eligible for the trial. To prevent contamination bias and promote treatment compliance, we decided to change the randomization unit from the individual to the motor vehicle. Consequently, all passengers from the same vehicle are randomized to the same study arm. We have observed that less than 5% of vehicles have multiple passengers. Therefore, our original sample size of 444 participants remains valid.

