**Methods and Design:**

We designed a pragmatic randomized clinical trial. A total of 444 participants (148 in each of three arms) who reside in Southern Ontario, Canada will be recruited from a large insurer. We will include individuals who are 18 years of age or older and who are diagnosed with Grade I or II Whiplash-associated Disorders. Participants will be randomized to physician-based education and activation or one of two rehabilitation programs of care currently in use in Ontario. Our primary outcome, self-rated global recovery and all secondary outcomes (neck pain intensity, whiplash disability, health-related quality of life, depressive symptomatology and satisfaction with care) will be measured at baseline by a trial coordinator and at 6 weeks, 3, 6, 9 and 12 months follow-up by an interviewer who is blind to the participants' baseline characteristics and treatment allocation. We will also collect information on general health status, other injuries, comorbidities, expectation of recovery, work status, pain coping, legal representation, and co-interventions. The primary intention-to-treat analysis will compare time to recovery between the three interventions. This trial will have 90% power at an alpha of 0.05 to detect a 20% difference in the rate of perceived recovery at one year. Secondary analyses will compare the health outcomes, rate of recurrence and the rate of adverse events between intervention groups.

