Our primary objective is to determine whether education and activation by a physician is more effective than two rehabilitation programs of care ("Soft Tissue Injury Care Model" developed by AVIVA Canada and the "Pre-approved Framework Guideline for Grade I and II Whiplash Associated Disorders" developed by the Financial Services Commission of Ontario, an arm's length agency of the Ontario Ministry of Finance) in improving recovery from WAD.

Our secondary objectives will compare the effectiveness of the three interventions on reducing neck pain intensity, reducing whiplash-related disability, improving the health-related quality of life, reducing depressive symptoms, improving satisfaction with care, shorten insurance claim durations, and reducing the recurrence rate in patients with WAD.

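### The 90% power at two-sided 0.05 is stated for the trial but holds at best for each pairwise comparison; power to show physician care better than both programs is about 83%

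*Protocol article*

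**What the plan says.** The Sample size section gives one calculation: "Our sample size was selected to detect a difference of 20% in the rate of recovery at one year using a log rank test", with "a power of 90% and a two-tail significance level of 0.05". It continues: "Based on these parameters, we need 114 participants per group". After the loss allowance the target is 148 per arm, 444 in all. The section does not say which comparison this covers, or how many.

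The abstract (Methods and Design) attaches the same figures to the study as a whole: "This trial will have 90% power at an alpha of 0.05 to detect a 20% difference in the rate of perceived recovery at one year".

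The primary objective, at the end of the Background, is to "determine whether education and activation by a physician is more effective than two rehabilitation programs of care". That is two comparisons, each with physician care on one side.

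The section on the primary outcome analysis (self-perceived recovery) plans two hazard ratios with 95% confidence intervals, both with the Pre-approved Framework (PAF) arm as reference: physician care against PAF, and the Soft Tissue Injury Care Model against PAF. Physician care against the Soft Tissue Injury Care Model, which the objective needs, is not listed. The article names no overall test, no testing order, no division of alpha, and no rule on whether physician care must beat one program or both.

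**The concern.** A three-arm trial with two primary comparisons has more than one error rate and more than one power. A reader of the abstract will take 90% and 0.05 as the trial's chance of answering its question and its chance of a false positive. If the figures describe a single pair, neither follows. The error across two tests depends on how they are combined, and the power to show superiority to both programs is below the power to show superiority to one. The sample size is fixed in this document, so what it can deliver for the stated objective should be clear here.

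**Working it through.** **Inputs.** From the article: three equal arms; two-sided 0.05; 90% power; 114 per group; 148 per arm enrolled; 30% loss. Assumed: approximately normal test statistics and equal information per arm. Two contrasts that share an arm then have correlation 0.5, because each has variance 2σ²/n and their covariance is σ²/n.

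**The plan's own figure.** The article does not give the reference recovery rate or say whether 20% is absolute, so 114 cannot be derived from the stated inputs alone. Unadjusted two-group log-rank formulas give it under assumed rates. With (1.960 + 1.282)² = 10.507:
- Freedman, 20% against 40% recovered: hazard ratio ln(0.6)/ln(0.8) = 2.289; events = 10.507 × (3.289/1.289)² = 68.4; n = 68.4/(0.2 + 0.4) = 114.0 per group.
- Schoenfeld, 50% against 70%: hazard ratio ln(0.3)/ln(0.5) = 1.737; events = 4 × 10.507/(ln 1.737)² = 137.9; n = 137.9/1.2 = 114.9 per group.

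At alpha 0.025, a figure near 114 also arises for about 60% against 80% (Schoenfeld 112, Freedman 118). The number alone therefore does not prove an unadjusted pairwise calculation; the stated 0.05 points that way. Below, the standardized difference is set so that one comparison at 114 per group has exactly 90% power: θ = 1.960 + 1.282 = 3.242.

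**Error when two contrasts are each tested at 0.05.** 1 − P(|Z₁| < 1.96, |Z₂| < 1.96) with correlation 0.5 = 0.091. For all three pairs it would be 0.122, but the analysis section lists only two contrasts.

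**Power to beat both programs, each test at 0.05.** No alpha split is needed. With both true differences equal to the design difference, P(Z₁ > 1.96, Z₂ > 1.96) with means 3.242 and correlation 0.5 = 0.832. For 90% joint power the mean would have to be 3.537, that is 114 × (3.537/3.242)² ≈ 136 per group.

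**Power if beating either program suffices and error is controlled.** Bonferroni at 0.025 each (critical value 2.241):
- one named comparison: Φ(3.242 − 2.241) = 0.841;
- at least one of the two: 0.938.

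**Three-arm test first (2 degrees of freedom, 0.05), then pairwise tests at 0.05.** With three arms, any two true pairwise nulls imply that all three arms are equal, so this is a closed procedure and family-wise error stays at 5%.

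| True pattern | Three-arm test | One full-difference pair, gated | Physician care beats both, gated |
|---|---|---|---|
| Physician care better than both equally | 92.8% | 87.9% | 82.9% |
| Third arm midway | 83.5% | 82.9% | about 36% |

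In the first row, gated power to beat both is almost the ungated 83.2%. In the second, one of the two differences is only half the design difference, and that is why joint power is low; without the gate it is also about 36%.

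**Lower bound for loss.** 148 × 0.7 = 103.6 per arm. If those lost contribute nothing, the mean becomes 3.242 × √(103.6/114) = 3.090, which gives 87.1% for one comparison and 78.8% for both. The analysis censors dropouts at their last completed interview, so they do contribute, and these are worst-case values.

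**The case against.** The strongest reply is that nothing stated is shown to be false. The article nowhere promises family-wise control or power to win both comparisons; read per comparison, 90% and 0.05 can both stand. This is correct, and it rules out a stronger inference that a reader might draw: that the pair fails under every reading of the objective. It does not. If beating either program suffices, Bonferroni at 114 per group keeps error at or below 5% with 93.8% power for at least one win, and the gated procedure gives 92.8%, when physician care is better than both equally.

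A reader might also infer from the 9% that the trial would name a false best treatment at about twice the nominal rate. The documents do not support that. To name one arm best, it must beat both others. With all arms equal and unadjusted pairwise tests this happens about 1.4% of the time, and about 5% with two arms tied for best and the third clearly worse. The 9% counts any significant difference in either direction. The objective is directional, and the chance of falsely finding physician care better than at least one program is about 4.5%.

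A further reply is that a testing rule commonly sits in the analysis plan, which is not shown. So the absence of a rule is not an error in itself. But a rule placed there would not turn the unqualified figure in the abstract into the power for superiority to both programs. That a two-group calculation was used is also inferred, as shown above.

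**Conclusion.** The point holds as a matter of labelling and of power for the stated objective. The 90% at 0.05 is a per-comparison statement at best, presented as a property of the trial. Two contrasts sharing an arm, each tested at 0.05, carry a two-sided family-wise error of about 9%. If the objective means superiority to both programs, error is not inflated, but power is about 83% rather than 90%.

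The 83% assumes that one comparison truly has 90% power, that both true differences equal the design difference, and that arms are equal in size. If those lost to follow-up gave no data it would be about 79%, which is a lower bound. The article does not show that the 90% and 0.05 are wrong for a single comparison.

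**What to change.** 1. In the Sample size section and the abstract, say that 90% at two-sided 0.05 is per pairwise comparison, before any gate.
2. Add that power to show physician care better than both programs is about 83% when both true differences equal the design difference.
3. In the primary analysis, test the three arms with a 2-degree-of-freedom log-rank or Wald test at 0.05, and read pairwise tests at 0.05 only if it is significant. Include physician care against the Soft Tissue Injury Care Model among the reported contrasts, so that the analysis matches the objective.

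The cost is a few sentences and no added participants. The price of the gate should be stated: single-pair power falls from 90% to about 88% if physician care differs equally from both programs, and to about 83% if the third arm lies midway. Power to beat both is almost unchanged (82.9% against 83.2%). Raising that joint power to 90% would instead take about 136 per group before the loss allowance.

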### Pilot study

We conducted a pilot study from February 1 – 25, 2008. The purpose of the pilot study was to test the feasibility and implementation of the trial. Specifically, we aimed to: 1) determine the referral rate from AVIVA Canada; 2) determine the participation rate; 3) test the administration of the baseline questionnaire; 4) ensure that the interventions can be delivered in a timely fashion and according to the protocol and 6) determine the 6- week follow-up rate.

The trial coordinators received 41 referrals during the pilot study for a referral rate of 1.6 calls per day. Of those, 36 were eligible and 12 consented to participate (participation rate = 33.3%). Our baseline and follow-up questionnaires were well received by participants. The six week follow-up rate was 58.3% (7/12). One participant dropped out of the study to receive care at another clinic and four participants could not be reached to complete the follow-up interview. The interventions were delivered without any difficulties.

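### The 30% loss allowance was added as 114 × 1.3 = 148 per arm; keeping 114 after 30% loss needs 114 / 0.7 = 163, so 90% power is not secured under the stated allowance

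*Protocol article*

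**What the plan says.** The Sample size section of the protocol article sets out to "detect a difference of 20% in the rate of recovery at one year using a log rank test", with "a power of 90% and a two-tail significance level of 0.05". It concludes: "Based on these parameters, we need 114 participants per group". The next sentence adds the allowance for loss: "Assuming a 30% loss-to follow-up per arm we aim to enroll a total of 444 participants (148 per intervention arm".

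The abstract repeats the enrolment target ("A total of 444 participants (148 in each of three arms") and attaches the power to it without condition: "This trial will have 90% power at an alpha of 0.05 to detect a 20% difference".

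Two other places bear on the point. The analysis section for the primary outcome censors participants who drop out before recovery at their last completed interview and uses no imputation. The Pilot study section reports: "The six week follow-up rate was 58.3% (7/12".

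**The concern.** An allowance for loss should leave the required number after the loss has happened. Here the 30% was added to the required 114. It was not taken from the number enrolled. The two operations differ, and the one used gives too small a target for the loss rate stated in the same sentence.

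The abstract gives 90% power as a property of the 444-participant trial. If the comparison of the programs of care shows no difference, readers will judge that result by this figure. It should follow from the plan's own inputs, and with a 30% loss on the convention used it does not.

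**Working it through.** **Inputs, all from the protocol article.** Required number per group: 114 (Sample size). Loss: 30% per arm (Sample size). Enrolment: 148 per arm, 444 in total (Sample size and abstract). Power 90%, two-sided alpha 0.05, log-rank test (Sample size).

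**Step 1: reproduce the plan's figure.** 114 × (1 + 0.30) = 148.2, which rounds to 148, and 3 × 148 = 444. Both stated figures are reproduced.

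**Step 2: apply the loss to those enrolled.** 114 / (1 − 0.30) = 162.9, so 163 per arm and 3 × 163 = 489 in total. That is 15 more per arm and 45 more overall. Check: 163 × 0.70 = 114.1, which meets the requirement.

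**Step 3: what 148 leaves.** 148 × 0.70 = 103.6, about 104 per arm and 10 short of 114. The loss that 148 does cover is 1 − 114/148 = 23.0%.

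**Step 4: power if lost participants count for nothing.** Take the plan's own anchor, 114 per group = 90% power. For a log-rank comparison with unchanged recovery rates, the expected test statistic grows with the square root of the number per group. Hence

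power(n) = Φ[(1.960 + 1.282) × √(n/114) − 1.960].

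- n = 114: 90.0% (the anchor).
- n = 103.6: √(103.6/114) = 0.953, so Φ(1.130) = 87.1%.

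This scaling does not need the reference-arm recovery rate, which the article does not state.

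**Step 5: power if drop-outs contribute until they leave.** This step needs assumptions that are not in the document: exponential recovery, and a 30% loss spread exponentially over the year. Interviews are at 6 weeks and 3, 6, 9 and 12 months, as planned, and a recovery counts only if the participant is still followed at the next interview. With s the proportion not recovered at one year in an arm, and visit times t₁ to t₅ in years (t₀ = 0),

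expected events = 148 × Σ over arms and visits of (s^tₖ₋₁ − s^tₖ) × 0.70^tₖ.

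The reference is 114 per arm with no loss, which gives 114 × (2 − s₁ − s₂) events and is taken as 90% power. The ratio of events replaces n/114 in the formula of Step 4.

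| Not recovered at one year | Events, 148 per arm with spread loss | Events, 114 per arm without loss | Power |
|---|---|---|---|
| 0.10 vs 0.30 | 201.9 | 182.4 | 92.7% |
| 0.30 vs 0.50 | 148.1 | 136.8 | 92.1% |
| 0.40 vs 0.60 | 122.5 | 114.0 | 91.9% |
| 0.50 vs 0.70 | 97.5 | 91.2 | 91.8% |

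So at 30% loss, power is about 87% when all the loss precedes any outcome interview and about 92% when it is spread in this way.

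**The case against.** The strongest defence is that the primary analysis is a time-to-event analysis. Drop-outs are censored at their last completed interview. Someone who leaves after several interviews contributes time at risk, and someone who reports recovery before leaving contributes an event. On that view, 104 is not the number analysed and 87% is not the power. Step 5 supports this: with loss spread over the year, 148 per arm reaches about 92%.

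This stands as a limit on the consequence. It does not repair the calculation. The sample-size section did not model censoring. It inflated the 114 for loss, which makes sense only if lost participants do not count, and the inflation was then done wrongly. A participant lost before the six-week interview has no follow-up outcome to contribute, and nothing in the article says that loss will come later.

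A reader might go further and use the pilot, where 5 of 12 (41.7%) were not followed at six weeks, to claim a still lower power. The document does not support that. Only one of the five is reported as having dropped out. The other four could not be reached for that interview and might have answered later ones. With 12 participants, the exact 95% interval for the proportion not followed runs from 15% to 72%, which includes 30%. The pilot is a caution that 30% may be optimistic, and no power figure should be built on it.

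**Conclusion.** The enrolment figure is wrong as written for the loss rate stated beside it. The target of 148 per arm matches a complete loss of 23%, not 30%; the size that matches 30% is 163 per arm. On the plan's own sizing convention, power per pairwise comparison is about 87%, roughly 3 points below the stated 90%. This rests on taking 114 = 90% as correct and on the lost 30% contributing no outcome data.

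The shortfall is modest and conditional. A reader might infer that the trial certainly misses 90%, but the censoring rule does not allow that conclusion. The supported statement is that 90% is not secured under the stated allowance.

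Two further inferences should not be drawn. The sentence affirming that 444 remains valid answers a different question, the change to randomizing by vehicle, and says nothing about loss. The unstated reference recovery rate is detail that an article may leave to the full protocol, and the finding does not depend on it.

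**What to change.** Keep 444 and correct the statement in the Sample size section and the abstract: 148 per arm gives 90% power if up to 23% per arm contribute no outcome data, and about 87% per pairwise comparison if 30% contribute none. A clause may add that later drop-outs contribute censored follow-up, so 87% is the lower figure for a 30% loss. If the authors prefer to claim 90% power with 30% complete loss, the matching target is 163 per arm, 489 in total. The pilot's six-week follow-up may be cited as a caution about the 30%, without a power figure.

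Restating costs a sentence in two places and a slightly less favourable power claim. It needs no extra participants and no change to the analysis. The alternative costs 45 more participants.
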